## Abstract

**Background:**

Disparities in sexually transmitted infections (STI) are an urgent problem among Native American youth and young adults which are not fully explained by different sexual or related behaviors. These sexual health disparities are more likely attributed to social environments and structural determinants such as a shortage of sexual healthcare providers, lower socioeconomic status, and access barriers to STI screening and treatment, including geographic isolation and confidentiality concerns. Innovative, non-clinic based alternatives to promote STI screening and treatment are essential for alleviating these disparities. Self-care, or the care taken by individuals towards their own health and well-being may be such a strategy. This study will assess the efficacy of a self-care intervention, called Protecting Our Future Generation, for increasing uptake of STI screening and impacting sexual risk and protective behaviors among Native American youth and young adults living in a reservation-based community in the Southwestern United States.

**Methods:**

The proposed study is a randomized controlled trial to test the efficacy of a self-care intervention compared to a control condition. Participants will be Native Americans ages 14–26 years old who have had vaginal or anal sex at least once in their lifetime. Participants will be randomized to the intervention which includes: 1) a sexual health self-assessment with embedded clinical prediction tool predicting STI positivity, and 2) personalized messaging with key steps to lower risk for STIs, or the control condition which includes: 1) a self-assessment about water, soda and sugar sweetened beverage consumption, and 2) personalized messaging to meet recommended daily intake. All participants will be offered a self-administered STI test. Participants will complete assessments at baseline, 3- and 6-months follow-up. The primary outcome measure is completion of STI screening.

**Discussion:**

Protecting Our Future Generation is among the first self-care interventions uniquely focused on sexual health among a Native American population, who endure significant sexual health disparities and are under-represented in research. If efficacious, the intervention will be a model of sexual health self-care for Native American youth and young adults adaptable for use in healthcare and community-based settings.

**Trial registration:**

Clinical Trials: http://clinicaltrials.gov; NCT03895320; Registered 03/28/2019.

## Background

Disparities in sexually transmitted infections (STI) are an urgent problem among Native American (Native) youth and young adults. Nationwide, in 2017, the Chlamydia rate among Native Americans was 47.7% higher than the general population (781.2/100,000 vs. 528.8/1000) and rates of Chlamydia rose 3.7% among Natives between 2013 and 2017 [1]. Further, Natives had the second highest Gonorrhea rate among all races/ethnicities in 2017 [1].

Native young adults and adolescents suffer from high rates of Gonorrhea, with a rate of 561.9/100,000 for those between ages 15–19, and 926.6/100,000 for those between ages 20–24; these rates are 4.2 and 3.6 times the rate among Whites, respectively [1]. In 2013, in Arizona, where this study will take place, Native American females ages 20–24 endured the highest rates of Chlamydia among any demographic in Arizona, at 7767/100,000, which is 1.5 times the rate for Native females of the same age nationwide (5310/100,000) [2]. Additionally in Arizona, from 2012 to 2013 the greatest increase in Gonorrhea rates were among Native Americans (23%) [2].

Research attempting to explain this gap in STIs indicates a higher prevalence of STIs among Native youth and young adults is not fully explained by different sexual or substance use behaviors [3]. These disparities in sexual health by ethnicity may be better attributed to social environments and structural determinants such as a shortage of sexual healthcare providers, socioeconomic status, and access barriers to healthcare including confidentiality concerns, and geographic isolation [4–10]. Further, because many STIs can be treated free of charge within the Indian Health Service (IHS), differential access to screening and treatment may explain these disparities [3]. Data from IHS corroborate inequalities in access to care, namely underutilization of services by higher risk groups and a lack of universal promotion of sexual health care by providers [4, 11].

Innovative, non-clinic based alternatives to traditional sexual health screening and treatment are essential for alleviating these sexual health disparities. Promotion of self-care, or the care taken by individuals towards their own health and well-being may be such a strategy; it is endorsed for improving sexual health outcomes by increasing access to care and individual satisfaction with care through client-driven, confidential options [4, 12–16]. Improving sexual health though the promotion of self-care is increasingly a focus of preventing sexual health disparities due to: 1) increased availability of new technologies, 2) the ease of STI screening using non-invasive samples, and 3) the lack of capacity for routine sexual health care service provision common in many reservation-based and other rural communities [13].

Approaches that focus on self-care may also address budgetary limitations at IHS by maximizing case finding through selective screening of individuals at highest risk, aiding in risk communication with providers, and stimulating health-seeking behavior [4, 12–16]. Self-care approaches can also include strategies for identifying those at increased risk for STIs, and have potential for reducing onward transmission and preventing new cases of disease [15, 16]. Risk prediction or clinical prediction rules are tools that provide estimates of absolute risk based on a combination of several individual characteristics and are a nuanced approach to sexual health self-care [14–16]. Specifically, a brief self-assessment including a clinical prediction rule and corresponding personalized messaging may: 1) help an individual gain knowledge of their own risks; 2) stimulate health-care seeking behavior such as STI screening and treatment; and 3) grow patient efficacy for taking charge of their sexual health.

Many sexual health care interventions are developed from risk or deficits-based perspectives [17–21]. An alternative, protective factors-based approach, such as that rooted in Asset Theory, would instead focus on the strengths, assets and resources of individuals and their connections within their community [22]. With regard to youth and young adults, a focus on internal knowledge, attitudes, and positive behavioral choices, in addition to connection with pro-social peers and adults, communication with parents and other family members, and involvement in community activities may bear greater import and impact on sexual health outcomes of interest [17, 22, 23]. A focus on the aforementioned assets and resources may drive positive changes in sexual health by motivating individual attitudes to avoid negative health outcomes and providing strategies to utilize available health care [17, 22–25]. Such an approach is compatible with Native views of health and well-being which focus on strengths and a balance between physical, social, emotional and environmental health [18–21, 26]. Past research conducted with youth, including Native American youth, supports this idea and shows a predictive relationship between youth’s strengths and resources and the protective sexual health outcomes of abstinence, delayed sexual initiation, and use of birth control [22, 23].

### The current study

A self-care intervention including self-assessment and personalized messaging, grounded in Asset Theory, may motivate the protective sexual health behavior of STI screening. Specifically, risk prediction tools delivered through a self-assessment and corresponding personalized messaging have the potential to be powerful decision aids and should be evaluated using experimental study designs. This study will assess the efficacy of a self-care intervention, called Protecting Our Future Generation (POFG), for increasing uptake of STI screening and impacting sexual risk and protective behaviors, psychosocial assets, and resources. This paper describes the intervention Protecting Our Future Generation and protocol for its implementation and evaluation.

### Study aims

This study will be conducted in the southwestern U.S. with Native American youth and young adults (ages 14–26) residing in a rural, reservation-based community. We will conduct a two-arm randomized controlled trial to evaluate the POFG program for impacts on STI screening uptake, sexual health risk behaviors and protective sexual health practices. The primary research questions include: 1) Does POFG increase STI screening uptake; 2) Does POFG increase condom use at last sex; and 3) Does POFG decrease number of new sexual partners. Secondary research questions include exploring what participant variables impact the primary outcome of STI screening uptake, including: 1) sexual health knowledge, efficacy and intentions; 2) substance use; 3) psychosocial assets and resources; and 4) experiencing past symptoms of a STI.

## Methods/design

### Study overview and hypotheses

We will conduct a two-arm randomized controlled trial (RCT) to test the efficacy of the POFG self-care intervention for impacting participant uptake of STI screening, in comparison to a control group. POFG includes a brief self-assessment to predict absolute STI risk and corresponding personalized messaging. We hypothesize participants who receive POFG will have a higher rate of STI screening completion at 3-months follow-up, compared with participants who receive the control program. We will measure STI screening uptake at 6-months follow-up to see if any increases were maintained over time. We hypothesize that POFG will increase protective behaviors among participants by: i) helping youth and young adults gain knowledge of their own sexual health risks, assets and resources; ii) motivating protection of those assets and resources; and iii) encouraging good health practices and making responsible choices. We hypothesize the effects of POFG on STI screening uptake will be mediated by participant’s substance use and past STI infection. See Fig. 1 for an illustration of the flow of participants through the study.

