### Intervention

Protecting Our Future Generation (POFG) is a self-care intervention rooted in Asset Theory [17–25]. POFG provides participants with an opportunity to assess their own sexual risk and protective behaviors, understand their personal risk for current or future STI infection, receive tailored strategies and recommendations to engage in protective sexual health practices, and motivate completion of non-clinic based STI screening. The self-assessment includes questions pertaining to sexual health risk and protective behaviors and a valid clinical prediction tool established to predict STI positivity [16]. The personalized messaging describes key steps the person can take to lower their risk for STIs. The quiz with resulting score and personalized messaging will take approximately ten minutes to complete and be delivered via tablet at the first study visit. POFG participants will be offered a self-administered, non-clinic based STI testing kit (for *Neisseria gonorrhea*, *Chlamydia trachomatis* and *Trichomonas vaginalis*) after receiving their personalized messages.

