### STI treatment

For participants who opt to take the STI testing kit (intervention or control) they can: 1) complete it and return it to a study staff immediately, 2) take the test with them, complete it at a later time and drop it off at the designated study office, or 3) complete it at a later time and coordinate with a study staff to have it picked up at a location they choose.

All participants (intervention and control) who test positive for a STI will receive an assisted referral to a Public Health Nurse at IHS with whom we have partnered on this study to ensure all participants who test positive for one or more STIs receive timely and high-quality treatment.

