### Measures

The following assessments will be completed by participants: the standardized *Youth Health Risk Behavior Inventory* which has been previously adapted and piloted with Native American youth and young adults yielding Cronbach’s alphas ranging from 0.74–0.93; and the standardized *Youth Asset Survey*, with established reliability and validity among a random sample of 1350 youth (10% of which were Native; Cronbach’s alpha > 0.61) [17, 27, 28]. These two self-report surveys will collect information on participant demographics, sexual risk and protective behaviors, including STI screening uptake, as well as psychosocial assets and resources. All survey items were piloted with ten youth and young adults from the participating community (3 males and 7 females) ranging in age from 14 to 24 years; edits were made as necessary. See Table 1 for a complete description of measures.

**Table 1 Tab1:** Protecting Our Future Program Evaluation Measures

Measures	Description of Measure
Youth Health Risk Behavior Inventory	Assesses sexual behavior and related risk factors through close-ended questions that asks about STI and sexual behavior history, knowledge, intentions and attitudes. Adapted from Stanton and colleagues [27].
Youth Asset Survey	Assesses youth assets (knowledge, attitudes, future aspirations, use of time, health practices and responsible choices (role models, communication with parents and adults, community involvement and access to health care). Adapted from Oman and colleagues [17].

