### Statistical analysis

Study hypotheses will be tested using an “intent to treat” analysis. Baseline characteristics will be compared between groups using chi-square tests for binary or categorical outcomes, and Wilcoxon rank-sum tests for continuous outcomes. For the primary outcome of STI screening uptake, the proportion of participants completing screening (i.e. returning a test to study staff) by the 3-month study visit will be compared across groups using a chi-square test or log-binomial regression if participant characteristics are found to vary at baseline between groups. For all analyses, participants who drop-out during the study and don’t provide at least 3-month follow-up data will be removed from the analysis. If at 3- or 6-months follow-up the POFG intervention shows efficacy for increasing STI screening uptake, we will conduct mediation and moderation analyses to explore what factors may be impacting the efficacy of POFG to change STI screening behavior.

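### Past STI infection cannot mediate a single-visit intervention, and for the 3-month outcome the direction of any mediation through substance use is not identified

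*Protocol article*

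**What the plan says.** All references are to the protocol article.

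- **Study overview and hypotheses** names two mediators: "We hypothesize the effects of POFG on STI screening uptake will be mediated by participant’s substance use and past STI infection".
- **Intervention**: the POFG quiz, score and messages take about ten minutes and will "be delivered via tablet at the first study visit". The test kit is offered "after receiving their personalized messages". **Control condition** has the same sequence.
- **STI treatment** gives three ways to return a kit. One is to "complete it and return it to a study staff immediately"; the other two are later drop-off and later pick-up. No shares are given.
- **Primary outcome** and **Statistical analysis** count a kit returned to study staff between baseline and the 3-month visit.
- **Study visits and data collection** places surveys at baseline, 3 months and 6 months only. **Secondary outcomes** lists alcohol and drug use with a 3-month recall.
- **Measures** describes the survey that would supply infection history as one that "asks about STI and sexual behavior history, knowledge, intentions and attitudes".
- **Study aims** lists substance use and "experiencing past symptoms of a STI" among participant variables that may affect uptake. It does not call them mediators.
- **Statistical analysis** says that, if efficacy is seen at 3 or 6 months, "we will conduct mediation and moderation analyses to explore what factors may be impacting the efficacy of POFG". It does not say which variables are to be tested as mediators and which as moderators.

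**The concern.** A mediator has to be something the intervention can change, and the change has to come before the outcome. Past STI infection, in its ordinary sense, fails the first condition. Substance use can meet it only if measured after the messages, and for the primary outcome no survey falls between the messages and the close of the outcome window.

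What is at stake is the mechanism claim. An indirect effect reported through past infection would present baseline imbalance as mechanism. One reported through 3-month substance use could equally be behaviour that changed because of testing: a participant who tests positive is referred to a Public Health Nurse, for example.

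**Working it through.** The protocol states no figure for this hypothesis, so there is none to reproduce. The check sets the timeline against the two conditions and then gauges size.

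**1. Timeline for the 3-month primary outcome**

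| Measure | Can POFG change it? | Before kit return? |
|---|---|---|
| Past STI infection, as history before the first visit | No | Yes |
| Past STI infection, as reported at follow-up | Possibly, including through the kit result | Not established |
| Baseline substance use | No | Yes |
| 3-month substance use (recall of the past 3 months) | Yes | Not established: the recall covers the return window |

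No row meets both conditions. For a same-day return, the use recalled at 3 months essentially follows the outcome. For a return late in the window, most of it comes before.

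**2. Past infection: expected value and noise**

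Indirect effect = a × b, where a is the arm difference in the mediator and b its association with screening within arm. For a trait fixed before randomisation, E(a) = 0, so the expected indirect effect is 0 for any b.

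Noise, with 225 per arm (Participant randomization and study sample size) and two assumptions, past-infection prevalence p and b = 0.15: SD(a) = √[2p(1−p)/225], and SD of the indirect effect ≈ 0.15 × SD(a).

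- p = 0.10: SD(a) = √(0.18/225) = 0.0283; × 0.15 = 0.0042
- p = 0.25: SD(a) = √(0.375/225) = 0.0408; × 0.15 = 0.0061
- p = 0.40: SD(a) = √(0.48/225) = 0.0462; × 0.15 = 0.0069

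A simulation with the same inputs (4,000 trials each) agreed. The mean indirect effect was within 0.0001 of zero, with SDs of 0.0047, 0.0064 and 0.0071. The arm-to-mediator test was significant at the 5% level in 4.7% to 5.0% of trials, as chance predicts.

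For scale, the planned effect is 20% × 0.5 = 10 points to 25% × 0.5 = 12.5 points. One SD of noise is therefore about 4% (0.0047/0.125) to 7% (0.0071/0.10) of the planned effect, in either direction, with no mechanism behind it.

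**3. Substance use: size of a reversed path**

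Assume no true mediation, uptake of 22.5% versus 33.75% (a control rate inside the planned range, times 1.5), and substance use of 50% without early testing. Let f be the share of completed kits returned early, and d the drop in later use after an early return.

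- a = −f·d × (0.3375 − 0.225) = −0.1125·f·d
- Average within-arm variance of uptake = (0.225 × 0.775 + 0.3375 × 0.6625)/2 = (0.1744 + 0.2236)/2 = 0.1990
- Within-arm variance of use ≈ 0.25, so b ≈ −f·d × 0.1990/0.25 ≈ −0.8·f·d
- Spurious share of the total effect = a·b/0.1125 ≈ 0.8·(f·d)²

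With f = 0.25, d = 0.10: 0.8 × 0.025² = 0.05%. With f = 0.75, d = 0.20: 0.8 × 0.15² = 1.8%. Simulation over this range gave 0.1% to 1.9%. The artefact is non-zero but small under these inputs, none of which the protocol supplies. Common causes of substance use and screening were not modelled.

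**The case against.** The strongest reply is that this is one loose word in an exploratory plan. The analysis runs only if efficacy is shown, moderation is already planned beside mediation, and Study aims uses predictor wording for the same kinds of variable. The survey wave that supplies the mediator, and the mediation model, are details an article may leave to a fuller document.

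Much of that stands, and it rules out several stronger readings that a reader might infer:

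- **That the mediation analysis as a whole cannot answer its question.** Statistical analysis does not confine it to these two variables, and for screening after the 3-month survey, 3-month substance use would come first.
- **That many kits come back early, or that essentially all returns precede the behaviour measured.** No shares are given. The survey date follows the returns, but the behaviour recalled overlaps them, so order is ambiguous rather than reversed.
- **That the indirect effect through past infection is exactly zero in the analysed data.** Zero is the expectation under randomisation. Participants without 3-month data are removed, so selective dropout could disturb balance.
- **That Study aims repeats the error.** It makes no mediator claim.

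What does not stand is that the planned moderation analysis cures the problem. The hypothesis names past infection as a mediator, and nothing in Statistical analysis reassigns it. The choice of wave does not rescue substance use either: for the 3-month outcome, baseline comes too early to be changed by POFG and 3 months overlaps the outcome.

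**Conclusion.** The point holds in two parts of unequal strength.

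**Past STI infection** is wrongly named as a mediator. Read as history before the first visit, the only sense the text suggests, its expected indirect effect under randomisation is zero at both 3 and 6 months. Read from follow-up surveys, it could be a consequence of screening.

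**Substance use**, for the 3-month primary outcome, has no measurement that POFG could have changed and that is known to precede kit return. The direction is not identified. A large bias is not shown: the illustrative range is 0.1% to 1.9% of the total effect, on assumed inputs.

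Neither part touches the primary comparison of screening proportions, the sample size or the primary outcome definition. The harm is limited to a mechanism claim in an exploratory, conditional analysis, but the claim is stated as a study hypothesis and is worth correcting.

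**What to change.** Reword the hypothesis in Study overview and hypotheses along these lines: *Baseline past STI infection and baseline substance use will be examined as moderators of the POFG effect on screening uptake (arm-by-baseline interaction).* This falls under the moderation analysis already planned in Statistical analysis. Drop past STI infection as a mediator.

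If 3-month substance use is still analysed as a mediator of the 3-month outcome, report it as exploratory and associational, with no causal claim.

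Moving mediation to screening between 3 and 6 months is not a ready substitute. The protocol defines no such outcome, and restricting to people who had not screened by 3 months would condition on post-randomisation status, so the arms would no longer be compared as randomised.

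Cost: a change to one hypothesis and one clarifying sentence, with no new data, because the baseline survey already asks about these topics. The price is precision. If V is the variance of the overall arm difference and the moderator splits the sample in half, the interaction contrast has variance of about 2V + 2V = 4V, twice the standard error, and more if the split is uneven. Interaction estimates should be given with confidence intervals and read as exploratory.
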